## Abstract

**Introduction:**

First post-contrAst SubtracTed (FAST) MRI, an abbreviated breast MRI scan, has high sensitivity for sub-centimetre aggressive breast cancer and short acquisition and interpretation times. These attributes promise effective supplemental screening. Until now, FAST MRI research has focused on women above population-risk of breast cancer (high mammographic density or personal history). DYAMOND aims to define the population within the population-risk NHS Breast Screening Programme (NHSBSP) likely to benefit from FAST MRI. The study population is the 40% of screening clients aged 50–52 who have average mammographic density (BI-RADS (Breast Imaging Reporting and Data System) B) on their first screening mammogram. DYAMOND will answer whether sufficient numbers of breast cancers, missed by mammography, can be detected by FAST MRI to justify the inclusion of this group in a future randomised controlled trial.

**Methods and analysis:**

Prospective, multicentre, diagnostic yield, single-arm study with an embedded qualitative sub-study: all recruited participants undergo a FAST MRI. An internal pilot will assess the willingness of sites and screening clients to participate in the study. Screening clients aged 50–52, with a clear first NHSBSP mammogram and BI-RADS B mammographic density (by automated measurement) will be invited to participate (recruitment target: 1000). The primary outcome is the number of additional cancers detected by FAST MRI (missed by screening mammography). A Fleming’s two-stage design will be used as this allows for early stopping after stage 1, to save participants, funding costs and time continuing to the end of the study if the question can be answered earlier.

**Ethics and dissemination:**

The NHSBSP Research and Innovation Development Advisory Committee and the Yorkshire and Humber–Sheffield Research Ethics Committee (23/YH/0268, study ID (IRAS): 330059) approved this research protocol. Participation involves a two-stage informed consent process, enabling screening for eligibility through automated mammographic density measurement. Patients with breast cancer helped shape the study design and co-produced participant-facing documents. They will disseminate the results to the public in a clear and meaningful way. Results will be published with open access in international peer-reviewed scientific journals.

**Trial registration number:**

ISRCTN74193022

STRENGTHS AND LIMITATIONS OF THE STUDYProspective, multicentre design with defined study population and sample size determined by power calculation.Integrated quality assurance programme to optimise and standardise intervention image quality.DYAMOND First post-contrAst SubtracTed (FAST) MRI (FAST MRI) readers credentialed and certificated with an evaluated and standardised FAST MRI interpretation-training programme, using standard breast MRI interpretation benchmarks.Intervention acceptability to participants assessed using an embedded qualitative substudy.Single-arm study with limited collection of comparator data.

## Introduction

 Despite effective treatments, 30 women die from breast cancer every day in the UK.^1^ Early detection of breast cancer offers the best chance of survival^2^ and is the aim of the NHS Breast Screening Programme (NHSBSP) which offers mammographic screening to women aged 50–70 every 3 years and screens 2.12 million women/year in England.^3^

Mammographic screening programmes, including NHSBSP, result in overdiagnosis (detection of cancers which would not have caused harm during a woman’s lifetime) and underdiagnosis (failure to prevent a continued incidence of stage 2–4 breast cancers).^4 5^ Furthermore, interval cancers,^6^ which present symptomatically between screening rounds, comprise 30–44% of all breast cancers within the NHSBSP screened population.^6^,^8^ Later stage diagnosis of cancers, undetected at mammographic screening, confers a higher chance of morbidity from metastatic breast cancer and its treatment, and ultimately of mortality.^2^ This effect is compounded by mammography’s disproportionate failure to detect small, aggressive grade 3 cancers.^9^ It has been estimated that over 57 000 people in the UK are living with metastatic breast cancer and the knowledge that their cancer is incurable.^10^ Reducing breast cancer stage at detection is an important healthcare goal.

First post-contrAst SubtracTed MRI (FAST MRI) is an abbreviated breast MRI scan designed as a screening test^11^ to overcome some shortcomings of mammography, including poor sensitivity for small aggressive cancers.^911^,^13^ FAST MRI is quicker to acquire and interpret (cost and capacity benefits) than the gold standard breast screening modality, dynamic contrast-enhanced breast MRI (DCE-MRI). In the UK, DCE-MRI is currently reserved to screen only women at very high risk of breast cancer.^3 14 15^ Systematic reviews and meta-analyses have found no statistical difference in either sensitivity or specificity for cancer detection between DCE-MRI and FAST MRI, although currently a low level of evidence suggests FAST MRI could be as accurate as DCE-MRI.^13 16^ FAST MRI therefore holds promise to save more lives if used for a wider group of women than those currently screened with DCE-MRI.^11 13^

To date, research worldwide has focused on offering supplemental/additional imaging with a more sensitive imaging test (such as DCE-MRI or FAST MRI) only to women at above population risk of breast cancer, including the subset of the general population with high mammographic density.^17^,^21^ High mammographic density both increases a woman’s risk of breast cancer and increases the chances of a cancer being undetected by mammography.^17 22 23^

Worldwide, the American College of Radiologists’ Breast Imaging Reporting and Data System (BI-RADS) mammographic density classification is used to define breast composition.^24^ BI-RADS defines four density categories: A, B, C and D, where A is the least dense category and D the densest. At the age of first mammogram for population screening within NHSBSP (50–52 years), the percentage of women in each density category is approximately A: 10%, B: 40%, C: 40% and D: 10%.^25^ As breast density generally reduces in the years following the menopause,^26^ B category may be considered the ‘average’ breast density for women screened within the UK’s population-risk screening programme for breast cancer (aged 50–70).^27^

Density-determined risk-adaptive strategies that offer supplemental screening with DCE-MRI or FAST MRI, either for women with category D breasts or for those in categories C and D, result in higher cancer detection rates, a reduced incidence of stage 2 and greater breast cancers, and reduced interval cancer rates.^17 18 20 21^

However, there is insufficient evidence for the average density group (Bs) as to whether the addition of FAST MRI will be of sufficient benefit to warrant further investigation of this group in a phase III trial. This group, which makes up approximately 40% of the screened population, is excluded from other supplemental screening trials despite a knowledge gap about whether supplemental screening could benefit them.

The aim of this diagnostic yield study is to determine whether FAST MRI could detect sufficient breast cancers, missed by screening mammography, for screening clients aged 50–52 with average breast density (category B), to justify their inclusion in a future effectiveness and cost-effectiveness randomised controlled trial (RCT) of FAST MRI.

## Methods and analysis

This study protocol (Version 4.2 (26FEB2025)) is reported using the SPIRIT (Standard Protocol Items: Recommendations for Interventional Trials) reporting guidelines.^28^
Table 1 displays the study’s trial registration data.

**Table 1 T1:** Trial registration data

Data category	Information
Trial registration	ISRCTN74193022
Date of registration	30 September 2024
Other identifying numbers	NIHR150502 (funding) NBT_5273 (sponsor), IRAS 330059 (HRA) 23/YH/0268 (REC) CPMS ID 59828 (NIHR RDN)
Source of funding	Efficacy and Mechanism Evaluation Programme, an MRC and NIHR partnership (NIHR150502)
Sponsor	North Bristol NHS Trust
Contact details	[name] [contact]
Public title	Testing whether a FAST MRI scan can detect breast cancers which were not detected on mammograms, in women with average breast density

FAST MRI, First post-contrAst SubtracTed MRI.

### Study design

FAST MRI: DYAMOND is a prospective, multicentre diagnostic yield, single-arm study of FAST MRI with an embedded qualitative substudy to examine intervention acceptability.

A 9-month internal pilot phase, from first participant recruitment, has been incorporated into the trial to assess the willingness of clinicians and screening clients to participate. The progression criteria from this phase use a traffic light system based on site opening, recruitment and compliance as detailed in Table 2.

**Table 2 T2:** The 9-month internal pilot phase progression criteria

Threshold	Red	Amber	Green
Trial recruitment (% of the predicted recruitment at 6 months)	<65%	≥65%	≥100%
Number of sites opened	<2	≥2	4
Total number of participants recruited	<137	≥137	≥210
Compliance with FAST MRI (turning up for FAST MRI scans once booked)	<90%	≥90%	≥95%

FAST MRI, First post-contrAst SubtracTed MRI.

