### Statistical analysis

#### Sample size calculation

From previous studies, in population-risk screening clients aged 50–54 of all mammographic densities having their first screening mammogram (prevalent round), standard mammography finds approximately 7.5 cancers per 1000 women screened^38^ (there are no reported figures specific to age 50–52). The addition of MRI may detect an additional 16.5 per 1000 women screened^20^ in women with mammographically dense breasts (density category D^24^). Meta-analyses have shown that sensitivities and specificities for FAST MRI did not differ significantly from those for DCE-MRI,^13 16^ but confidence in the evidence was low and FAST MRI may not pick up as many cancers as DCE-MRI.^9^

A Fleming’s two-stage design^39^ will be used to assess the number of additional cancers detected by FAST MRI. This design allows for early stopping after stage one, which would save patients, funding costs and time continuing to the end of the study if the question could be answered earlier. Based on previous research and consensus from radiologists, health economists and public and patient involvement (PPI) representatives, 4 additional cancers detected per 1000 women screened was deemed the minimum that would be required to be detected to warrant further investigation of this study population in a phase III trial. Setting the lower limit for the cancer detection at 0.004 (4 additional cancers detected per 1000 women screened), the target rate at 0.011, 80% power and a 5% one-sided significance level, then a minimum of 959 participants would be required (381 participants at the first stage). Thus, recruiting 1000 participants to the study will allow for 4% dropouts.

An interim analysis will be performed when 381 participants have been recruited. If one or no additional cancers are detected, the study may be halted for futility. If five or more cancers are detected, then the study may be stopped early as it has already been shown that the inclusion of this population in a phase III trial is warranted. Otherwise, the study will continue, and eight or more additional cancers are required to be detected by the end of the study to warrant inclusion of this population in a future phase III trial.

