### Key study dates

Greenlight for recruitment start: 4 April 2025

Recruitment of first participant (time of first FAST MRI scan): 22 May 2025

Recruitment is anticipated to take 8 months to the recruitment target of 1000 participants.

Grant end date is 31 October 2026.

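### The 9-month internal pilot and its green count of 210 do not fit the stated 8 months to recruit 1000 participants

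*Protocol article*

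**What the plan says.** Four statements in the protocol article bear on this.

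- **Study design, text:** "A 9-month internal pilot phase, from first participant recruitment, has been incorporated into the trial". Its stated purpose is to gauge how willing clinicians and screening clients are to take part.
- **Study design, Table 2:** the title refers to 9 months. The first row is labelled "Trial recruitment (% of the predicted recruitment at 6 months", with red below 65%, amber from 65% and green from 100%. The count row reads "Total number of participants recruited <137 ≥137 ≥210".
- **Key study dates:** "Recruitment of first participant (time of first FAST MRI scan): 22 May 2025". Then "Recruitment is anticipated to take 8 months to the recruitment target of 1000 participants", and "Grant end date is 31 October 2026".
- **Sample size calculation:** "a minimum of 959 participants would be required (381 participants at the first stage"), with 1000 recruited to allow for dropout. Also, "An interim analysis will be performed when 381 participants have been recruited".

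No section explains how the pilot length and counts relate to the 8-month recruitment period.

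**The concern.** A pilot with red, amber and green criteria is there to inform a decision to continue, adapt or stop while that decision still matters. On the article's own dates the pilot ends after the last planned participant has been recruited. Its green count also appears to come from a different, much slower projection than the one behind the 8 months. Table 2 adds a further ambiguity, because the title and the first row point to different months.

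What is at stake is whether the Trial Steering Committee can use Table 2. On the fast timetable the criteria are met almost at once and reviewed too late. On the slow one the review is timely, but a green result says little about whether the study can reach its required size within the funded period.

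**Working it through.** **Inputs.** Pilot 9 months; counts 137 and 210; prediction at month 6 (Study design, Table 2). 1000 participants in 8 months; first participant 22 May 2025; grant end 31 October 2026 (Key study dates). 959 required, interim at 381 (Sample size calculation). Linear accrual is assumed unless stated.

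**1. Where the counts come from.** 0.65 × 210 = 136.5, rounded up to 137. So 210 behaves as the 100% prediction and 137 as 65% of it. The article does not say so, but the match is close.

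**2. The 8-month timetable.**
- Rate: 1000 / 8 = 125 a month.
- Recruitment would end about 22 January 2026 and the pilot about 22 February 2026, one month later.
- Expected by month 6: 6 × 125 = 750. Green is 210 / 750 = 28% of that.
- Time to reach 137: 137 / 125 = 1.1 months. To reach 210: 210 / 125 = 1.7 months. To reach the interim at 381: 381 / 125 = 3.0 months.

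**3. Could a slow start explain 210?** Going from 210 at month 6 to 1000 at month 8 needs (1000 − 210) / 2 = 395 a month, about 11 times the 35 a month before it. If four sites open 1 to 2 months apart (an assumption), a path that reaches 1000 at month 8 still has about 600 to 690 by month 6. Accrual growing with the square of time gives 1000 × (6/8)² ≈ 560. None comes near 210.

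**4. The timetable that 210 implies.** From 22 May 2025 to 31 October 2026 is 527 days, or 527 / 30.44 = 17.3 months.

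| 210 read at | Rate per month | Months to 1000 | Recruited by grant end |
|---|---|---|---|
| Month 6 | 210 / 6 = 35 | 28.6 | 35 × 17.3 ≈ 606 |
| Month 9 | 210 / 9 = 23.3 | 42.9 | 23.3 × 17.3 ≈ 404 |

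Rate needed for 959 by the grant end: 959 / 17.3 ≈ 55 a month. This is a lower bound, since it leaves no time for reading, assessment or analysis.

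**5. Reading Table 2 as it stands.** If the prediction in the first row is 210, the first row and the count row say the same thing. If it is the 8-month plan (about 750 at month 6), 210 recruited is red in the first row (28%) and green in the count row.

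**6. The main design.** The exact two-stage calculation (381 then 959; stop at 1 or fewer or at 5 or more; success at 8 or more) gives a one-sided error of 0.048 at 4 per 1000 and power of 0.803 at 11 per 1000. Allowing 4% dropout, 959 / 0.96 ≈ 999. The target of 1000 is sound; the conflict is confined to the timetable.

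**The case against.** The strongest objection is that the two harms need different accrual rates and cannot both occur. At 125 a month the pilot reports too late, but there is no shortfall. At 35 a month the month-9 review falls at about 9 × 35 = 315 participants, before the interim at 381, and can still change the study. This stands. A reader might infer that the progression criteria cannot work at all; the document does not support that.

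A reader might also infer a large loss of power. With 606 participants and the cut-off of 8 kept, power at 11 per 1000 is 0.48. That is only an illustration. It assumes linear accrual up to the last day of the grant, everyone scanned, and a cut-off derived for 959. At 606 that cut-off gives a one-sided error of only 0.021; a cut-off of 6 gives 0.042 and power 0.66. The figure describes a hypothetical scenario and is not a property of the plan.

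Three further points limit the concern.
- Table 2 is not the only control. Under Trial oversight the data monitoring committee reviews recruitment and the steering committee decides on continuation.
- The site-opening and compliance rows do not depend on the accrual rate, although a month-9 decision on them would be equally late on the 8-month plan.
- The pilot is described as a test of willingness to take part, not as proof that 959 can be reached. Even so, a row set at 100% of predicted recruitment needs a prediction that agrees with the rest of the plan.

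The article gives no explicit start for the 8 months and does not show the projection. Counting from the greenlight of 4 April 2025 widens the gap. Placing the 8 months after the pilot is not what the text says, and would still need 790 / 8 ≈ 99 a month after 23 a month.

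**Conclusion.** The inconsistency is real and rests on printed figures. The pilot outlasts planned recruitment by a month, and the green count is 28% of what the 8-month plan predicts for month 6 under linear accrual. The plausible ramp-ups tried do not close the gap. If accrual follows the green count instead, the review can take place in time, but green is compatible with about 606 or 404 recruited by the grant end, against 959 required. These totals assume a constant rate from first participant to grant end.

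The point is a should-fix. It concerns the feasibility criteria and the timeline only; the primary outcome, sample size, stopping boundaries and analysis are not affected.

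**What to change.** Derive the pilot length, the Table 2 counts and the recruitment duration under Key study dates from one dated recruitment projection. In particular:

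- use the same assessment month in the Table 2 title and in its recruitment row;
- place that assessment before planned recruitment ends;
- set the green count at the number the projection predicts for that month, on a path that reaches 959 scanned within the funded period, and amber at 65% of it if that fraction is kept;
- if 210 is the true prediction, replace the 8-month estimate and state how 959 will be reached before 31 October 2026.

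The cost is an edit to one table and to the key dates, with the agreement of the steering committee and the funder. No extra participants are needed.

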#### Study objectives

The primary objective is to measure the number of additional cancers detected by FAST MRI that were missed by screening mammography. The study objectives are detailed in Box 1.

Box 1FAST MRI: DYAMOND study objectivesPrimary objectiveTo measure the number of additional cancers detected by FAST MRI that were missed by screening mammographySecondary objectivesTo assess the characteristics of cancer detected by FAST MRI (including type, grade, size, stage, nodal involvement and other characteristics linked to prognosis and benefit or harm from screen detection)To determine the acceptability of the intervention through questionnaire and an additional qualitative interview of a subset of participantsTo analyse recruitment rates, retention rates, recall rates, biopsy rates, early call rates and any adverse reactions to FAST MRITo streamline the prospective digital categorisation of mammographic density using NHS-owned software (Scientific Computing Department of the RSNFT)To determine the proportion of screening clients in each density category (A, B, C, D) in the (UK) NHSBSP screened population at this ageTo create a dataset of mammograms and corresponding FAST MRI scans with known outcome having potential use in future training and research, for example, for analysis with artificial intelligence/machine learningTo collate a central pathology database of the cancers detected for future translational researchTo collect data to enable a micro-costing exercise to extend the previously conducted budget impact analysis^43^To explore data linkage for longer term outcomesFAST MRI, First post-contrAst SubtracTed MRI; NHSBSP, NHS Breast Screening Programme; RSNFT, Royal Surrey NHS Foundation Trust.

#### Study setting

The NHSBSP units within the UK are eligible to take part as recruiting sites, provided they can screen their clients for participation and offer a FAST MRI scan (and follow-up if required).

A list of recruiting study sites is available on the FAST MRI: DYAMOND website (https://www.nbt.nhs.uk/research-development/our-research/current-research/breast-care-research-hub/fast-mri-research-programme/taking-part-fast-mri-dyamond-study).

#### Participant eligibility criteria

Participant recruitment to DYAMOND entails a two-stage eligibility and consent process, as summarised in Box 2.

Box 2FAST MRI: DYAMOND two-stage consent processStage 1 Consent (breast density measurement)Inclusion criteriaAge* (49 years + 8 months) ≤ (53 years – 1 day) at time of mammogram (source: NBSS)Has had a mammogram via the NHSBSPWilling and able to give informed consent to stage 1Exclusion criteriaHas not received a mammogram within the NHSBSPAged (<49 years + 8 months) or ≥53 years at time of mammogram (source: NBSS)Unwilling to have mammograms measured for densityUnwilling or unable to give informed consent to stage 1Breast implantsStage 2 Consent (FAST MRI DYAMOND scan)On receipt of breast density measurement for participants recruited to stage 1, participants will be screened for eligibility at stage 2.Inclusion criteriaFirst screening mammogram (prevalent round) (source: participant-reported)Participants with breast density category B as determined by AI breast density measurement (source: Scientific Computing Department of the RSNFT)Received standard NHSBSP ‘no findings’ confirmation letter (source: NBSS)No absolute contraindication to breast MRI (source: patient-reported, via completion of Standard Safety Questionnaire)Exclusion criteriaBreast density category (A, C or D or if not determined) (source: RSNFT)Known recall after mammogram (source: NBSS)Pregnant or breastfeedingContraindication to MRI**Contraindication to gadolinium-containing contrast agents.Unwilling to have FAST MRIUnwilling to allow follow-up of outcomes through data-linkageEstimated glomerular filtration rate equal to or below 30 (participant reported)BMI, weight and abdominal girth restrictions may apply to recruiting sites’ MRI scanner(s) that could exclude otherwise eligible participants from having the study intervention* Age range NHSBSP invites for first screening mammogram.** Participants found to have conditional contraindications to MRI will be reviewed by the local Radiology service and advice given as to the actions required to facilitate an MRI to take place, in line with local guidelines and best practice. If it is not possible to reasonably adjust for the situation in question, by following local policy, the referral to FAST MRI will be rejected and the participant will not be eligible for a FAST MRI.BMI, body mass index; FAST MRI, First post-contrAst SubtracTed MRI; NBSS, National Breast Screening System; NHSBSP, NHS Breast Screening Programme; RSNFT, Royal Surrey NHS Foundation Trust.
